## Abstract

**Introduction:**

Esophagectomy in the prone position can induce acute respiratory acidosis. While it is known that metabolic acidosis can significantly elevate serum potassium, the effect of respiratory acidosis is conventionally considered to cause minimal or no elevation. However, clinical practice in this surgical setting sometimes reveals a greater-than-expected degree of hyperkalemia. The objective of this study is to investigate the association between this acute respiratory acidosis and hyperkalemia, and to explore its clinical implications.

**Methods and analysis:**

This is a retrospective, two-center observational study of adult patients who underwent thoracoscopic esophagectomy in the prone position at two major Japanese institutions between January 2022 and December 2024. The primary outcome is the mean difference in serum potassium levels between the supine (baseline) and prone-position phases, analyzed as a paired-design within each patient. Key secondary outcomes include: 1) a multivariable analysis to identify factors associated with the magnitude of potassium increase; 2) a sensitivity analysis of the primary outcome after excluding cases with significant metabolic acidosis (e.g., base excess < −5 mmol/L); and 3) correlation analyses between the change in potassium and various physiological parameters, including PaCO₂ and markers of metabolic stress. Analyses will include the paired t-test, correlation analyses, and multivariable regression models.

## Introduction

Prone positioning has become an increasingly common approach for thoracoscopic esophageal cancer surgery to facilitate surgical exposure. It has been associated with better surgical outcomes and improved perioperative safety compared to the classical lateral decubitus position [1]; however, it may significantly impact ventilation. Partial lung collapse and intrathoracic insufflation of carbon dioxide (CO₂), commonly used in these procedures, may contribute to significant alterations in respiratory physiology and acid-base balance.

Clinically, elevations in serum potassium levels associated with acute respiratory acidosis are often observed during these surgeries. While acidosis is generally known to affect potassium distribution, respiratory acidosis is typically considered to cause only minimal or no elevation in serum potassium compared to metabolic acidosis [2–3]. However, recent clinical reports challenge this view in the setting of critical illness; for instance, Pathak and Nanda described cases of severe, refractory hyperkalemia in COVID-19 patients where acute respiratory acidosis was identified as a major contributing factor [4]. Nevertheless, the combination of prone positioning, ventilatory compromise, and CO₂ insufflation may alter the expected physiological response.

The primary aim of this study is to quantify the magnitude of serum potassium elevation associated with acute respiratory acidosis during prone-position esophagectomy. Furthermore, we aim to explore the physiological drivers of this phenomenon, including the respective contributions of respiratory and metabolic factors. Ultimately, this research may contribute to enhancing the safety of ventilation strategies and optimizing electrolyte management for these complex procedures.

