### Outcomes

#### Primary outcome.

The mean difference in serum potassium levels between the baseline (supine) and the intraoperative (prone) timepoints.

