**Analyses of Factors Associated with Potassium Increase:**
**Correlation Analysis:** To explore potential physiological drivers, correlations between the change in serum potassium (ΔK⁺) and changes in other variables will be assessed. These variables will include the change in PaCO₂ (ΔPaCO₂) and markers of metabolic stress, such as the change in lactate (ΔLac).**Multivariable Analysis of** Δ**K** ⁺ **:** A multivariable linear regression analysis will be performed to identify factors independently associated with the magnitude of the serum potassium increase (ΔK⁺). Candidate covariates for the multivariable model include the change in PaCO₂ (ΔPaCO₂), change in lactate (ΔLactate), baseline eGFR, fluid balance, norepinephrine dose, and the duration of the prone position. The final selection of independent variables will be determined based on clinical relevance, assessment of multicollinearity (e.g., variance inflation factor), and the sufficiency of outcome events to avoid overfitting.

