#### Analysis for the primary outcome.

A paired t-test will be used to compare the mean serum potassium levels between the baseline and intraoperative timepoints.

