## Discussion

This study protocol was designed to address a critical clinical observation: a greater-than-expected elevation in serum potassium during prone-position esophagectomy. This finding stands in contrast to the conventional physiological understanding that respiratory acidosis—a common consequence of this procedure—causes minimal or no elevation in serum potassium, particularly when compared to metabolic acidosis [2–3]. Therefore, the primary objective of this study is first to confirm and quantify the mean increase in serum potassium between the supine (baseline) and prone-position phases. Given that acute respiratory acidosis is an almost inevitable event during this surgical phase, demonstrating a statistically significant potassium increase would, in itself, strongly suggest a clinically relevant phenomenon that challenges existing knowledge. However, we recognize that major surgery introduces multiple confounding variables that could influence potassium levels, such as metabolic stress. To address this complexity, our secondary analyses are designed to (1) assess the robustness of our primary finding via sensitivity analysis that controls for the effect of metabolic acidosis, and (2) explore the association between the potassium increase and various physiological drivers, including the severity of respiratory acidosis itself.

In particular, surgical techniques involving partial lung collapse and intrathoracic CO₂ insufflation may lead to rapid external CO₂ loading, resulting in acid-base changes distinct from those seen in endogenous respiratory acidosis. Multiple mechanisms, including H⁺/K⁺ exchange and altered ATPase activity, may contribute to this response. The body’s compensatory systems may not be able to fully respond to the acute rise in PaCO₂, potentially leading to more pronounced potassium fluctuations than typically expected.

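### The primary aim is the potassium rise associated with respiratory acidosis, but the primary outcome is the total baseline-to-prone rise, and the one planned estimate that could bear on the aim in mmol/L is not fixed

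*Protocol article*

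**What the plan says.** - **Aim (Introduction).** The primary aim is to "quantify the magnitude of serum potassium elevation associated with acute respiratory acidosis during prone-position esophagectomy". The same paragraph adds a further aim: to explore the drivers, including what respiratory and metabolic factors each contribute.
- **Primary outcome (Outcomes).** "The mean difference in serum potassium levels between the baseline (supine) and the intraoperative (prone) timepoints".
- **Primary test (Analysis for the primary outcome).** "A paired t-test will be used to compare the mean serum potassium levels between the baseline and intraoperative timepoints". There is no covariate and no comparison group.
- **Objective as restated (Discussion).** To "confirm and quantify the mean increase in serum potassium between the supine (baseline) and prone-position phases". The link back to respiratory acidosis is the premise "Given that acute respiratory acidosis is an almost inevitable event during this surgical phase", from which it follows, in the article's view, that "demonstrating a statistically significant potassium increase would, in itself, strongly suggest a clinically relevant phenomenon that challenges existing knowledge". The next sentences concede confounding and hand it to the secondary analyses.
- **Secondary analyses (Secondary outcomes).** A correlation of the potassium change with the PaCO₂ change, and a multivariable linear regression of the potassium change. On the latter: "Candidate covariates for the multivariable model include the change in PaCO₂", followed by lactate change, eGFR, fluid balance, norepinephrine dose and prone duration. Then: "The final selection of independent variables will be determined based on clinical relevance, assessment of multicollinearity", with avoidance of overfitting as a further criterion.
- **Sensitivity analyses (Secondary outcomes).** The primary outcome is repeated without patients whose base excess is below −5 mmol/L, and again only in patients with PaCO₂ of at least 50 mmHg.

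**The concern.** The aim names a part of the rise; the outcome measures all of it. The Discussion joins the two by noting that nearly every patient becomes acidotic in the prone phase. That argument does not help. When almost everyone is exposed, the before-after mean also contains everything else that changes between the two samples. The protocol itself collects several such items: fluids, transfusion, norepinephrine, lactate and time in the prone position.

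What is at stake is the meaning of the headline result. The conventional view that the study wants to test concerns respiratory acidosis specifically, and the Discussion carries the expected finding on to blood gas monitoring, permissive hypercapnia and intensive care. Those extensions need evidence that potassium tracks CO₂. A significant total rise does not supply it.

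**Working it through.** **Inputs from the protocol (Sample size estimation).** Mean rise 0.73 mmol/L, SD 0.53, from 50 preliminary cases; target about 150 patients. The section's minimum of 34 patients concerns the total rise only and plays no part here.

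**Inputs assumed, because the protocol gives no PaCO₂ distribution.** PaCO₂ change with mean 25 and SD 10 mmHg, baseline PaCO₂ 40 mmHg, and a linear effect. A wider range is used in step 4.

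**Step 1. The primary statistic.** t = 0.73 / (0.53/√150) = 0.73 / 0.0433 = 16.9. The 95% half-width of the mean is 0.086 mmol/L. No PaCO₂ value enters the formula, so the result cannot depend on how the rise divides. This holds by construction and needs no assumption about PaCO₂.

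**Step 2. What does respond to the CO₂ share.** If a share f of the mean rise goes linearly with PaCO₂, the slope is f × 0.73/25 per mmHg, or f × 0.292 mmol/L per 10 mmHg. Simulation (1,000 datasets of 150 patients for each share; total mean and SD held at 0.73 and 0.53; slope adjusted for lactate change) gave these averages:

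| CO₂ share | Mean rise | t | Adjusted slope per 10 mmHg | Mean rise, PaCO₂ ≥ 50 |
|---|---|---|---|---|
| 0% | 0.73 | 16.9 | 0.00 | 0.73 |
| 25% | 0.73 | 17.0 | 0.07 | 0.74 |
| 50% | 0.73 | 17.0 | 0.14 | 0.75 |
| 75% | 0.73 | 17.0 | 0.22 | 0.76 |
| 100% | 0.73 | 16.9 | 0.29 | 0.77 |

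The slope separates the cases; the primary mean does not.

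**Step 3. The sensitivity analyses.** Both are again mean rises within a subset. Restriction to PaCO₂ of at least 50 mmHg moves the mean only from 0.73 to 0.77 over the full range of shares, and no comparison with patients below 50 is planned. Excluding marked metabolic acidosis removes one competing explanation and leaves the others in the mean.

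**Step 4. Precision.** With the residual SD taken as 0.53 (the case where nothing tracks CO₂) and PaCO₂ change as the only predictor, the 95% half-width of the slope per 10 mmHg is 10 × 1.96 × 0.53 / (SD × √150):
- SD 8: 0.106 mmol/L
- SD 10: 0.085 mmol/L
- SD 15: 0.057 mmol/L

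Multiplying the slope by the mean PaCO₂ change would give an amount in mmol/L, with these half-widths:
- mean 15, SD 15: 1.0388 / (15 × 12.247) × 15 = 0.08
- mean 25, SD 10: 1.0388 / (10 × 12.247) × 25 = 0.21
- mean 35, SD 8: 1.0388 / (8 × 12.247) × 35 = 0.37

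So the range is roughly 0.1 to 0.4 mmol/L. At the upper end, an amount of 0 and an amount of half the rise (0.365) are not clearly separated. Covariates correlated with the PaCO₂ change would widen these figures.

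**The case against.** The strongest reply is that the protocol already divides the questions. The primary analysis describes the rise, and the drivers are a declared further aim served by a correlation and a regression in which the PaCO₂ change is the first candidate. Read that way, the aim may simply mean the rise seen during the acidotic phase. The Discussion concedes confounding straight after the disputed sentence and lists separation of respiratory and metabolic components as a limitation. A total as primary outcome with drivers studied secondarily is a legitimate descriptive design.

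Much of this stands. A reader might infer that no planned analysis addresses the CO₂-associated part. The document does not support that: an adjusted slope from the regression would address it, and a flat relation would show up there and in the correlation. What remains is that the correlation is not a magnitude, the regression need not keep the PaCO₂ term, and the Discussion draws its inference from the total before any of this is seen.

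A reader might also take slope times mean PaCO₂ change as an unbiased answer to the aim. It is not. Its good behaviour in simulation follows from data generated as linear and unconfounded. Take mean/SD settings of 15/8, 25/12, 25/8 and 35/15 mmHg. If the whole 0.73 is due to CO₂ but only above a 10 mmHg change, the product gives 0.96 to 1.28; with a square-root shape it gives 0.39 to 0.43. If the true part is zero, an unmeasured factor that explains 20% of the variance and correlates 0.3 with the PaCO₂ change produces 0.13 to 0.22 mmol/L.

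**Conclusion.** The point holds as a mismatch between the stated aim, the primary estimate and the inference drawn from it. The primary result is identical at every CO₂ share from 0 to 100%, and that conclusion rests only on the form of the test. The near-constancy of the PaCO₂ ≥ 50 mmHg subset (0.73 to 0.77) and the precision figures rest on assumed PaCO₂ distributions.

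It does not follow that the design is invalid, that the paired t-test should be dropped, or that the authors plan to report the full 0.73 mmol/L as caused by CO₂. The Discussion speaks of a clinically relevant phenomenon and acknowledges confounders. The defect is that the estimate most relevant to respiratory acidosis is left optional, while significance of the total is given a meaning that it cannot carry. This should be corrected before the analysis.

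**What to change.** 1. Describe the paired t-test as estimating the total potassium rise during the prone phase. Align the primary aim in the Introduction either with that total or with the slope on the PaCO₂ change.
2. Keep the PaCO₂ change in the linear model of the potassium change regardless of covariate selection. Report its adjusted slope in mmol/L per 10 mmHg with a 95% CI as the estimate that bears on respiratory acidosis.
3. Reword the Discussion so that statements about respiratory acidosis rest on that slope and not on the total being significant.

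Slope times mean PaCO₂ change may be added as an illustration only. It should be stated that it assumes linearity down to zero change and no residual confounding, and that its precision depends on a PaCO₂ distribution not yet known.

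The cost is small: wording and one fixed term in a model already planned, using data already to be collected. The Study status section says that extraction and analysis had not begun. The downside is that the slope is a between-patient observational association and may be less precise than the total.

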## Methods

### Study design

This will be a retrospective, two-center observational study.

### Study status

The study period covers patients treated between January 2022 and December 2024. While the clinical records for this period already exist, data extraction for this specific research purpose, as well as all statistical analyses, have not yet begun.

We plan to commence data collection (extraction) on or after December 1, 2025, with an estimated completion by March 2026. Authors will not have access to information that could identify individual participants during or after data collection, as all data will be fully anonymized prior to analysis. We anticipate that statistical analysis will be completed and results are expected by May 2026. This protocol is being registered and published prior to data access and analysis to ensure transparency and pre-specify the analytical plan, thereby minimizing the risk of outcome reporting bias.

### Participants

All adult patients who underwent esophageal cancer surgery, including robot-assisted procedures, in the prone position between January 2022 and December 2024 at Aichi Medical University Hospital and Aichi Cancer Center will be included. Patients with pre-existing chronic kidney disease (not requiring dialysis) are eligible for inclusion, and the influence of baseline renal function will be evaluated as a pre-planned subgroup analysis.

### Exclusion criteria

● Patients undergoing chronic dialysis ● Patients with severe electrolyte abnormalities (defined as a preoperative serum potassium level of 5.0 mmol/L or higher) ● Patients who received intraoperative massive transfusion (defined as having received a transfusion for a blood loss of 2000 mL or more).

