### Data collection

The following data will be collected from medical records: ● **Patient demographics:** Age, sex, BMI, ASA PS ● **Preoperative status:** eGFR, history of diabetes, hypertension, respiratory dysfunction or heart disease, perioperative use of diuretics, insulin, or β2-agonists. ● **Procedural details:** ○ Surgical approach (e.g., thoracoscopic, robot-assisted, or open thoracotomy) ○ Anesthesia method ○ Surgical time, Anesthesia time ○ Duration in the prone position ○ CO₂ insufflation (presence, duration, and pressure) ○ Bronchial blocker usage ● **Hemodynamics and fluid balance:** ○ The minimum mean arterial pressure (MAP) during the main surgical phase (prone phase) ○ Intraoperative urine output, Fluid volume, Blood transfusion status ○ Norepinephrine use and total dose ● **Arterial blood gas data:** ○ Serum potassium, pH, PaCO₂, HCO₃ ⁻ , BE, AG, and lactate will be collected at the following three timepoints: ■ **Timepoint 1 (Baseline):** After induction of anesthesia, before surgical positioning or incision. ■ **Timepoint 2 (Intervention):** During the phase of maximal respiratory challenge (e.g., the point of highest PaCO₂ during prone positioning with capnothorax). In cases where arterial blood gas was measured multiple times during the prone phase, the data from the timepoint with the lowest arterial pH will be used for the primary analysis. ■ **Timepoint 3 (Post-procedure):** Immediately upon arrival in the ICU or at the end of surgery.

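### The transfusion exclusion covers the whole operation and only losses of 2000 mL or more, so it does not match the Timepoint 1 to Timepoint 2 interval in which the primary potassium change is measured

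*Protocol article*

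**What the plan says.** Under Exclusion criteria, the protocol article removes "Patients who received intraoperative massive transfusion (defined as having received a transfusion for a blood loss of 2000 mL or more". Two conditions must both hold: a transfusion, and a blood loss of at least 2000 mL. The only limit on timing is that the transfusion was intraoperative.

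The primary outcome is "The mean difference in serum potassium levels between the baseline (supine) and the intraoperative (prone) timepoints". Under Data collection, the baseline sample (Timepoint 1) is taken once anesthesia is induced and before positioning. For the prone sample (Timepoint 2), where several gases exist, "the data from the timepoint with the lowest arterial pH will be used for the primary analysis". A third sample, not used in the primary outcome, is taken "Immediately upon arrival in the ICU or at the end of surgery".

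The transfusion and fluid items are listed as "Intraoperative urine output, Fluid volume, Blood transfusion status", with no timing relative to the samples. One neighbouring item is tied to the phase of interest: "The minimum mean arterial pressure (MAP) during the main surgical phase (prone phase".

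The primary analysis is unadjusted: "A paired t-test will be used to compare the mean serum potassium levels between the baseline and intraoperative timepoints". Besides the change in PaCO₂, the candidate covariates for the regression of the potassium change are "change in lactate (ΔLactate), baseline eGFR, fluid balance, norepinephrine dose, and the duration of the prone position". Transfusion is not among them.

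**The concern.** The protocol does not explain the exclusion. Its natural purpose is to keep potassium changes caused by transfusion and major bleeding out of an endpoint meant to reflect acute respiratory acidosis. For that, the rule has to act on what happens between the two samples, and as written it can err in both directions.

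- **Kept but exposed.** Red cells given between Timepoints 1 and 2 for a loss below 2000 mL do not trigger the exclusion. Any exogenous potassium is then part of the measured rise.
- **Dropped but unexposed.** Massive transfusion given only after Timepoint 2 does trigger it, although both endpoint samples had already been drawn. That is selection on an event after the outcome.

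This matters because of the weight placed on the raw change. The Discussion says that a statistically significant rise would by its own force point to a phenomenon at odds with current understanding. An inference of that strength needs an obvious non-respiratory source of potassium to be handled in the right interval. The stated aim is also to quantify the rise, so bias in the mean matters even where the test result is not in doubt.

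**Working it through.** **Step 1: the two intervals side by side.**

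| Situation | Excluded as written? | Can it affect the Timepoint 1-2 change? |
|---|---|---|
| Transfused between Timepoints 1 and 2, loss under 2000 mL | No | Yes |
| Transfused between Timepoints 1 and 2 for a loss of 2000 mL or more | Yes | Yes |
| Transfused only after Timepoint 2 for a loss of 2000 mL or more | Yes | No |
| Transfused only after Timepoint 2, loss under 2000 mL | No | No |
| Loss of 2000 mL or more, no transfusion | No | Not through transfused potassium |

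The first and third rows are the mismatches. The third can occur because Timepoint 2 lies in the prone phase and Timepoint 3 is at the end of surgery or on ICU arrival, so the operation can continue after the endpoint sample.

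**Step 2: does a later analysis correct it?** The paired t-test has no covariates. The two sensitivity analyses select on base excess below −5 mmol/L and on PaCO₂ of 50 mmHg or more, and neither refers to transfusion. The candidate covariates include fluid balance but not transfusion.

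**Step 3: possible size for patients kept but exposed.** The protocol states no figure on this point that could be reproduced, and the sample-size figure plays no part in it. The inputs below on exposure and added rise are assumptions. From Sample size estimation come the target of about 150 patients, the preliminary mean rise of 0.73 mmol/L and its SD of 0.53.

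Shift in the mean = k × e / 150, where k is the number of exposed patients kept in and e the extra rise in mmol/L:

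| k of 150 | e = 0.3 | e = 0.5 | e = 1.0 |
|---|---|---|---|
| 1 | 0.002 | 0.003 | 0.007 |
| 5 | 0.010 | 0.017 | 0.033 |
| 15 | 0.030 | 0.050 | 0.100 |

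Expressed as a share exposed: 0.05 × 0.3 = 0.015 and 0.15 × 0.5 = 0.075 mmol/L. Relative to the preliminary rise, 0.015 / 0.73 = 2% and 0.075 / 0.73 = 10%.

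For comparison, the half-width of the 95% confidence interval at 150 patients is t(0.975; 149) × 0.53 / √150 = 1.976 × 0.0433 = 0.086 mmol/L. In the table only the most extreme cell (15 patients, 1.0 mmol/L each) exceeds it.

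**Step 4: possible size for patients dropped but unexposed.** If m of N patients are dropped, the mean moves by (m / N) × (mean change of those kept − mean change of those dropped). This is zero unless late massive transfusion is related to the earlier potassium change. The documents give neither m nor that difference. Without such a relation, the only loss is a few patients.

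**The case against.** The strongest reply is that the effect is too small to matter. Even with exposure and added rise assumed without support from the documents, the shift is 2-10% of the preliminary rise and below the half-width of the confidence interval. The primary test would not be overturned. The protocol also acknowledges that major surgery brings several confounders, so it does not treat the raw rise as purely respiratory. Patients dropped for late transfusion are probably few. All of this stands and limits the weight of the point. It does not remove the mismatch, since the acknowledgment does not mention transfusion and no planned analysis addresses it.

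A reader might also infer more than the documents support:

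- *That the exclusion cannot be applied because blood loss is not in the data list.* That list also omits dialysis status and preoperative potassium, on which the other two exclusions turn. It is not a screening form. Eligibility can be checked in the existing records, and a journal article condenses such lists. The absence of a field for potassium given is likewise no finding.
- *That analysts could not repair the problem later.* Transfusion status is collected, so the primary analysis can be repeated without any transfused patient. The candidate covariate list does not bar transfusion status either, because final selection rests partly on clinical relevance.
- *That hypokalemic patients, whom the electrolyte criterion does not exclude, are likely to be given potassium between the samples.* Nothing in the documents says so.
- *That late bleeding alone leads to exclusion.* The rule also requires a transfusion.

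**Conclusion.** The point holds as a mismatch of intervals. As written, the rule keeps patients transfused between the two endpoint samples for a loss below 2000 mL, and drops patients massively transfused only after the second. Neither the primary analysis nor the planned sensitivity analyses correct this.

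The effect on the primary mean is probably small and cannot be quantified from the documents. The range of 0.015-0.075 mmol/L rests wholly on the assumed 5-15% exposed and 0.3-0.5 mmol/L added per exposed patient. Analyses that use individual values (the correlations, the regression of the potassium change, and the logistic model for potassium above 5.0 mmol/L) may be more sensitive to a few affected patients, but that cannot be sized either. The conclusion also assumes that the transfused product carries potassium, which the protocol does not discuss. The change is worth making because it costs little, and the protocol states that extraction had not begun.

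**What to change.** 1. Tie the exclusion to transfusion given between the Timepoint 1 and Timepoint 2 samples, and do not exclude patients whose transfusion came only after Timepoint 2. If a blood-loss threshold is kept within that interval, item 2 covers the patients below it.
2. Add a sensitivity analysis of the primary outcome, and of the regression of the potassium change, that omits patients given red cells, or intravenous potassium where recorded, between the two samples, whatever the blood loss.
3. If timing cannot be extracted, run that sensitivity analysis without all transfused patients, using the transfusion status already collected. This removes every red-cell load but does not restore patients dropped for late massive transfusion.

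The cost is one reworded criterion, slightly more abstraction from the anesthesia record, and a few fewer patients in the sensitivity analysis.
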